##### **3.2.4 Exploratory:**

- Evolution of pulmonary lesions on chest imaging,
- Evolution of biological parameters related to hemostasis, coagulation and inflammation,
- Determination of predictive factors for a response.

## 4. STUDY DESCRIPTION

### 4.1 STUDY DESIGN

A randomized, double blind, multicenter, placebo- controlled, parallel group, fixed dose, phase II study. The study evaluates the efficacy and safety of glenzocimab. Patients will be screened for eligibility and all tests should have results prior to any randomization, so as to avoid screening failures to a maximum extent. The turn-around time for these tests should be comprised within 24hrs to allow for early inclusions if needed. Eligible patients (n=68) will be randomized in a 1:1 ratio to glenzocimab or placebo. Patient inclusions will be fractioned into sequential (3-day apart) cohorts of growing size (2, 4 then 6 patients), each balanced between glenzocimab and placebo in order to check safety in a gradual manner.

Glenzocimab will be administered by IV infusion. The dosing regimen will be 1000mg over 6 hrs, every 24 hrs for 3 consecutive days. All patients will receive in parallel the best medical care at the discretion of the investigating center, or per local guidelines. Unless, patient's condition worsens after the first infusion and/or an untoward adverse drug reaction precludes it, the treatment should be readministered 24 hrs after the initiation of the first infusion, and likewise after the second infusion, so that a total of 3 subsequent infusions, that represent the expected standard treatment should be administered. The allocation of each patient in any given center to an active treatment or placebo will strictly follow a central randomization scheme. Clinical supplies allocation to centers should provide the necessary material so that any eligible patient can receive the assigned treatment. An IxRS will be used to manage randomization and drug shipment. The whole process will be handled in a manner that is blinded for the treatment received to all involved study personnel. The study period will be of a maximum of 40 days per patient. Patients will be closely monitored during the first 7 days following randomization with complete evaluations being performed at 24 hrs, 48 hrs, 72 hrs, then on Days 4 (96 hrs), 5 (120 hrs), and 7 (+/-1 day), 14 (+/-2 days), 20 (+/-2 days), 40 (+/-3 days). Should a patient being discharged before Day 40, a distant consultation should be undertaken if it is not deemed desirable that the patient comes back to the institution.

STUDY PROTOCOL

ACT-CS-006-GARDEN-V6.0 FINAL

[figure not shown]

### Figure 5: Study Design and Schedule of Visits

### Patient Safeguards and Early Stopping Rules

Decisions regarding patient's safety are primarily made by the principal investigator and/or under his/her responsibility. This could entail discontinuing the IV infusion, not undertaking the following infusion(s), prescribing any other treatments as warranted by patient's status or evolution, terminating patient's participation to trial. However, in this latter case, close follow-up should be undertaken, notably in the presence of unresolved SAE/SUSAR. In all case, the Sponsor should be informed urgently.

Safety data will be reviewed by an independent Data Safety Monitoring Board (DSMB).

- First review: the first safety review will occur after the first 12 patients enrolled have received 3 days of infusion and have been followed for 3 days after the last infusion.
- Second review: the second safety review will occur after the first 30 patients enrolled have received 3 days of infusion and have been followed for 3 days after the last infusion.
- Additional ad-hoc DSMB meetings may be set up on a need basis, in particular if SAEs/SUSARs were to be recorded, or in case of any unforeseen significant medical event that would warrant an informed safety judgment, as per DSMB charter.
- The Sponsor Medical Team will set up a procedure to monitor this study on an ongoing basis and closely coordinate with the PI, Steering Committee and DSMB in all safety matters.

## 4.2 STUDY DURATION FOR THE PATIENT

For each given patient, schedule will include:

- A screening assessment upon admission to ensure of diagnosis and inclusion criteria
- At Day 1:
  - a baseline visit followed by a randomization procedure, initiation of first infusion,
  - a post-infusion evaluation at 3 hrs (+/-1hr) after the end of administration.
- At Day 2:
  - Initiation of second infusion (pending results of prior evaluation)
  - A post-infusion evaluation at 3 hrs (+/-1hr) after the end of second administration if a second administration takes place.
- At Day 3:
  - Initiation of third infusion (pending results of prior evaluation)
  - A post-infusion evaluation at 3 hrs (+/-1hr) after the end of third first administration if a third administration takes place.
- At day 4: a follow-up evaluation at 96 hrs (+/- 3 hrs), post beginning of first administration (primary end-point recording).
- At day 5: a follow-up evaluation at 120 hrs (+/-3 hrs), post beginning of first administration.
- In case, the administration is not repeated, post-infusion evaluation at 3hrs at Day 2 and Day 3, Day 4 (96 hrs), Day 5 (120 hrs) visits should take place anyway.
- A follow-up visit at Days 7 (+/-1 day), 14 (+/- 2 days) and 20 (+/-2 days),

- A 40-day (+/-3 days) post-treatment final evaluation, (End-Of- Study visit).

Additional follow-up visits, or phone calls may be required on a need basis notably in case of emerging or prolonged adverse events. Remote visits utilizing specific devices can be undertaken if it is not desirable that the patient, if discharged comes back to the institution.

## **4.3 PREMATURE STUDY DISCONTINUATION FOR A PATIENT**

### **4.3.1 Discontinuation from Study Treatment**

The investigator may permanently terminate the treatment administration (during the course of any of the 3 IV infusions) at any time notably in case of an adverse event judged unacceptable or a worsening of patient's condition (for detailed procedure, please refer to [Section 6.3](#)). If the reason for discontinuation is an adverse event, the patient must be followed until resolution or stabilisation of the event (see [Section 9.6](#)). In the case of a needed concomitant IV administration of another drug, the study treatment administration might be temporarily suspended, taking carefully note of the infusion stop and re-start times; however, the global study treatment administration must not last beyond 7 hours, including the suspension time-intervals.

### **4.3.2 Discontinuation from the Study**

Patients have the right to withdraw from the study at any time for any reason. Considering the population of patients that will be included, an emergency inclusion process has been integrated to the protocol. In accordance with the requirement of this procedure patients will be asked to consent as soon as they become able to. If a patient decides to not consent at this point, follow-up assessments will be discontinued and therefrom:

- Data collection since the time the patient withdraws his consent will be permanently stopped.
- Data collected from the beginning of the patient's participation to study up to patient's withdrawal of consent will be analysed (except if this is not allowed according to local regulation).

### **4.3.3 Lost to Follow-Up**

Investigators should make every effort to minimize the number of patients lost to follow-up and to obtain all relevant information on those patients, particularly in the search of any AEs. All contact attempts will be documented in the patient's medical records.

## **4.4 END OF STUDY**

Trial termination will be defined as the last defined as last patient last visit and thus the trial is expected to last approximately 7,5 months (6 months of inclusion period plus 40 days of follow-up period). The Sponsor, in accordance with the Study Scientific Committee and/or the DSMB, may decide to stop the trial or part of the trial at any time.

The study may be stopped prematurely by the sponsor in accordance to the recommendation of the Scientific Committee or the DSMB if it is considered that the benefit/risk balance is no longer in favor of the patients (in regard with the study data or new data available coming from

other studies).

The study could also be stopped upon Health Authorities or IECs/IRBs request.

#### **4.5 INDEPENDENT DATA SAFETY MONITORING BOARD (DSMB) AND SAFETY REVIEWS**

An independent data safety monitoring board (DSMB) will be set up before the first enrolled patient.

The DSMB will include one clinician (expert in pneumology or infectious diseases), one clinical pharmacologist, and an expert statistician. All of them will be independent of the team in charge of the study conduct.

The primary objective of the DSMB is to review the safety data. At each review, the DSMB will review demographic, baseline, and safety data, including incidence rates of AEs and SAEs regardless of relatedness, events requiring the discontinuation of study drug, notable AEs and laboratory abnormalities, which will be summarized and tabulated by System Organ Class, preferred term, and severity grade prior to each meeting. Listings and/or narratives of “on-study” deaths and serious and significant AEs, including any early withdrawals due to AEs, will be provided. Data to be reviewed will be summarized by treatment arm and will include information on patient accrual, baseline characteristics, and key safety information.

Two safety review meetings are planned:

- First review : the first safety review will occur after the first 12 patients enrolled have received 3 days of infusion and have been followed for 3 days after the last infusion.
- Second review : the second safety review will occur after the first 30 patients enrolled have received 3 days of infusion and have been followed for 3 days after the last infusion.
- In addition to the scheduled meetings, **ad hoc DSMB meetings** for any safety issue can be hold on request of the glenzocimab study team (study investigators, Acticor and PV-CRO). In this regard, inclusions will be fractioned into sequential (3-day apart) cohorts of growing size, each balanced between glenzocimab and placebo in order to check safety in a gradual manner. In addition, a complete independent medical monitoring will occure after the 2 first patients, then the following 4 patients, then the next 6 patients.

Based on these safety data, the DSMB will make recommendations to the Sponsor as to whether the trial should continue without changes, be modified, or be stopped due to safety concerns. If the study is terminated early based on the DSMB recommendation, ACTICOR will notify the appropriate regulatory authorities.

Further details on the interim analyses and the responsibilities of the DSMB will be provided in the DSMB Charter.

## 4.6 OVERSIGHT COMMITTEES

A study scientific dedicated meeting was set up in order to validate the most important protocol choices.

Attendees were 1) clinicians from various countries, who have a strong recognized expertise in the field of infectious or pulmonary diseases, 2) Clinical pharmacologists and/or methodologists. During this meeting, there were also representatives from the Sponsor.

- 1) A Study Steering Committee comprised of members of the Sponsor, as well as a few of the Scientific Advisors, and the Study Global Coordinator will be responsible for the permanent study oversight. It is co-chaired by the Global Study Coordinator and [REDACTED], Infectious Diseases Specialist, Executive Medical Advisor to Acticor Biotech.

The Steering Committee may require the intermittent or permanent recourse to ad-hoc experts as needed.

### 4.6.1 Mission of the Study Steering Committee

The Study Steering Committee will be the oversight and decision body for this trial, though the liability for final decisions will remain that of sponsor, as per GCP and regulations.

The study steering committee will meet a need basis depending upon DSMB preconisation, and the necessity to discuss, make or endorse decisions. Should some face-to-face meetings be impossible to hold due to practical constraints, virtual (e.g. phone / webex) meetings should take place. In any case, whatever the modality, detailed minutes and decisions should be documented in writing.

The DSMB may ask specific questions to the Steering Committee, and vice-versa. In the event, rapid responses are required, Steering Committee Chairs should be contacted first. In any case, the DSMB will be responsible to preserve study integrity in its communicating to the Steering Committee, particularly so as the blind is maintained.

## 5. STUDY POPULATION

### 5.1 ELIGIBILITY CRITERIA

A total of 60 evaluable adult patients, hospitalized and presenting with acute respiratory distress syndrome that meet the following study criteria will be enrolled to the study.

#### 5.1.1 Inclusion Criteria

1. Male or female hospitalized patients  $\geq 18$  years (i.e., at least 18 years old at the time of randomization) and  $< 80$  years, having given their written consent.
2. Having a positive RT-PCR or antigenic test for COVID-19, or with a highly positive serology AND clear symptoms of COVID-19,
3. Presenting with symptoms of COVID-19, including:
  - Cough
  - OR

- Shortness of breath or difficulty breathing  
OR at least 2 of the following
  - Fever, defined as any body temperature  $38^{\circ}\text{C}$
  - Chills
  - Repeated shaking with chills
  - Muscle pain
  - Headache
  - Sore throat
  - New loss of taste or smell
4. Presenting with signs of moderate but progressive pulmonary disease in the last 48 hours with:
- Respiratory symptoms (cough, dyspnea, etc.),
  - Uni- or bilateral ground-glass opacities, or pulmonary infiltrates on chest radiograph and/or CT scan performed within the past 96hrs,
  - Clinical and/or biological evidence of progression over the past 48hrs.
  - Progression will be assessed as follows:
    - symptom worsening: increase in the number of symptoms, and/or in the intensity of some of them  
And/or
    - worsening of respiratory condition: increase in respiratory rate and/or decrease of  $\text{PaO}_2/\text{FiO}_2$  in ambient air  
And/or
    - worsening of biological markers: CRP increase or increase of other severity/prognostic markers, and/or increase of D-Dimers
5. Presenting with a **moderate** respiratory distress defined as:
- a) At least one of the following signs associated with the onset of ARDS:
- Respiratory rate (RR)  $\geq 24/\text{min}$ ,  
OR
  - $\text{SpO}_2 \leq 93\%$  in ambient air. In case where oxygenotherapy cannot be discontinued, please refer to NEWS 2 Scale (item  $\text{SpO}_2$ , scale 2) for adequate conversion (e.g. 93-94 on  $\text{O}_2$  corresponding to 86-87 in ambient air),  
OR
  - $\text{PaO}_2/\text{FiO}_2 \leq 200\text{mmHg}$  (please refer to Appendix 3 for conversion).
- AND**
- b) NOT in a **severe** respiratory distress defined as:
- Respiratory rate (RR)  $< 30/\text{min}$ ,  
And
  - $\text{PaO}_2/\text{FiO}_2 > 100\text{mmHg}$ .

6. Presenting with signs of a pro-thrombotic status characterized by:

- a. D-Dimers  $\geq 0.5 \mu\text{g/mL}$ ,
  - b. and/or Troponin T  $> 2.5 \mu\text{g/L}$  (or by default Troponin I greater than local laboratory reference),
  - c. and/or signs of micro-angiopathy on a vascular enhanced chest CT-scan. *(Thrombocytopenia  $< 150,000/\text{mm}^3$  or prolonged Prothrombin Time (PT)  $> 12\text{s}$  are additional signs of a pro-thrombotic status that are not necessary for eligibility).*
7. With one or more of the following biological markers of progression:
- CRP  $\geq 10 \text{ mg/L}$ ,
  - LDH  $> 250 \text{ U/L}$ ,
  - IL6  $> 8 \text{ pg/mL}$ ,
  - Lymphocyte count  $< 1 \cdot 10^9/\text{L}$ ,
  - NT proBNP  $> 88 \text{ pg/mL}$ ,
  - Pro-calcitonin  $> 0.5 \text{ ng/mL}$ ,
  - Ferritin  $> 400 \mu\text{g/L}$ ,
8. Effective birth control that should have been in place for at least 2 months in non-menopausal women and 4 months for men after IMP administration. Birth control methods considered to be highly effective include:
- Combined (estrogen-progestogen) hormonal contraception associated with the inhibition of ovulation: oral, intravaginal, transdermal,
  - Progesterone-only hormonal contraception associated with the inhibition of ovulation: oral, injectable, implantable,
  - Intrauterine device,
  - Intrauterine hormone-releasing system,
  - Bilateral tubal occlusion,
  - Vasectomized partner.
9. Women of child-bearing potential must have negative results of a urinary or plasma pregnancy test (serum HCG).

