| 
Safety endpoints
 | 
Secondary efficacy endpoints :
 
 
• All cause Death at day 40 and Overall Survival
 
• WHO-COVID-19 Scale
 
• NEWS-2 Scale
 
• Respiratory Rate status defined as:: 
 
○ Normal: < 20/min,
 
○ Mild: <math>20/\text{min} \leq \text{RR} < 24/\text{min}</math>,
 
○ Moderate: <math>24/\text{min} \leq \text{RR} < 30/\text{min}</math>,
 
○ Severe: <math>\geq 30/\text{min}</math>,
 
○ Death.
 
 
 
• Hypoxemia status defined as:: 
 
○ Normal: > 300 mmHg,
 
○ Mild: <math>200 \text{ mmHg} < \text{PaO}_2/\text{FiO}_2 \leq 300 \text{ mmHg}</math>,
 
○ Moderate: <math>100 \text{ mmHg} < \text{PaO}_2/\text{FIO}_2 \leq 200 \text{ mmHg}</math>,
 
○ Severe: <math>\text{PaO}_2/\text{FIO}_2 \leq 100 \text{ mmHg}</math>,
 
○ Death.
 
 
 
• SpO2 status defined as: 
 
○ Normal: > 95%
 
○ Mild: <math>93\% < \text{SpO}_2 \leq 95\%</math>,
 
○ Moderate: <math>90\% < \text{SpO}_2 \leq 93\%</math>,
 
○ Severe: <math>\leq 90\%</math>,
 
○ Death.
 
 
 
• Chest CT-Scan (or in exceptional cases, chest radiogram)
 
• Oxygen-free days (over the study period = 40 days),
 
• Need for mechanical ventilation,
 
• Mechanical ventilation-free days,
 
• Hospital-free days (over study period = 40 days),
 
• Clinical recovery and Time to Clinical recovery (over study period = 40 days),
 
• Cure and Time-to-cure (over study period = 40 days).
 

 
• Incidence, nature and severity of Adverse Events, SAEs, SUSARs and Treatment-Emergent Adverse Events (TEAEs),
 
• Incidence of bleeding-related events,
 
• Incidence of hypersensitivity reactions,
 
• Changes to vital signs over the course of the study versus screening,
 
 |

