### 11.1 General considerations

In general, summary tabulations will be presented by treatment arm and will display the number of observations, mean, standard deviation, median, minimum, and maximum for continuous variables, and the number and percent per category for categorical data. The Kaplan-Meier survival curves and 25th, 50th (median), and 75th percentiles will be provided along with their 2-sided 95% confidence intervals (CIs) for time-to-event data.

The nominal one-sided alpha level of significance considered for statistical tests will be 0.025.

As this is essentially an estimation study, no adjustment for multiplicity will be proposed.

Methods for handling missing data will be further detailed in the SAP.

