### 11.4 Sample Size Determination

As this is essentially an exploratory study which aim is to estimate the treatment difference in order to better design the future trials, the sample size cannot be justified on a formal power calculation based on a reasonable expected difference.

60 (sixty) patients are considered sufficient to estimate the treatment effect on the efficacy parameters.

As a rough order of magnitude, if the true death rate is assumed to be 0.4 in the placebo group, then a true death rate of 0.10 should be assumed to achieve at least a 80% power to detect this difference in rates at the 1-sided alpha level of 0.025, using an unpooled variance Z test. If the true death rate is assumed to be lower, such as 0.3 in the placebo group, then a true death rate of 0.04 should be assumed to achieve at least a 80% power to detect this difference in rates at the 1-sided alpha level of 0.025, using an unpooled variance Z test.

Assuming a dropout rate of 12%, 68 patients will be enrolled in this study.

With regard to the primary safety endpoint, 60 (2X30) patients randomized will be sufficient to observe in the ACT017 arm at least one serious adverse event which incidence is greater than or equal to 5% with a probability of at least 79%.

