**Secondary efficacy endpoints**

**All-Cause Mortality at day 40 (ACM20)**

Death rates will be estimated at day 40 within each group.

The difference in ACM20 rates and the odds ratio will be estimated along with their asymptotic and exact 95% confidence intervals. p-values from the chi-square and exact Fisher test will also be provided.

The All-cause mortality at Day 40 will also be analyzed in a Logistic regression model including treatment, BMI (>30 , <30) , Age (>60 , <60) and baseline respiratory distress status for each primary component (moderate or not). The adjusted odds ratio with its 95% CI for treatment will be estimated in this model.

Subgroup analyses will also be analyzed in the same logistic regression model including treatment, each factor (separately) and a term for treatment-by-factor interaction.

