|                                               | Intubation and mechanical ventilation                        | 6            |
|                                               | Ventilation + additional organ support – pressors, RRT, ECMO | 7            |
| Dead                            | Death                                                        | 8            |

*Appendix 3 : Conversion tables for estimation of PaO2 and FiO2*[figure not shown]**Instructions to complete the CRFs****Conversion tables****1 Estimating PaO2 from a given SO2**

| SO 2 (%) | PaO 2 (mmHg) |
|---------------------|-------------------------|
| 80                  | 44                      |
| 81                  | 45                      |
| 82                  | 46                      |
| 83                  | 47                      |
| 84                  | 49                      |
| 85                  | 50                      |
| 86                  | 52                      |
| 87                  | 53                      |
| 88                  | 55                      |
| 89                  | 57                      |
| 90                  | 60                      |
| 91                  | 62                      |
| 92                  | 65                      |
| 93                  | 69                      |
| 94                  | 73                      |
| 95                  | 79                      |
| 96                  | 86                      |
| 97                  | 96                      |
| 98                  | 112                     |
| 99                  | 145                     |

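### Moderate SpO2 has no lower limit at entry but stops above 90% in the endpoint scale, so the SpO2 covariate in the Day 40 mortality model is undefined and coarse (minor)

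*Protocol*

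**What the plan says.** Criterion 5 in Section 5.1.1 has two parts. Part (a) asks for at least one of three signs: respiratory rate of 24/min or more, SpO2 of 93% or less in ambient air, or PaO2/FiO2 of 200 mmHg or less. Part (b) requires that the patient is "NOT in a severe respiratory distress defined as" a rate below 30/min together with a PaO2/FiO2 above 100 mmHg. It contains no SpO2 term. For patients who cannot come off oxygen, the criterion refers to a conversion and gives one worked pair, a reading of 93-94 on oxygen "corresponding to 86-87 in ambient air". Criterion 5 in the synopsis bounds rate and PaO2/FiO2 on both sides and likewise sets no floor for SpO2.

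The secondary endpoints, in Section 9.1 and in the synopsis ("SpO2 status defined as"), divide SpO2 into normal (above 95%), mild (above 93 to 95%), moderate (above 90 to 93%), severe (90% or less) and death.

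Section 11.5.1 specifies a logistic model for Day 40 mortality with treatment, BMI, age and "baseline respiratory distress status for each primary component (moderate or not") as covariates. It does not say which definition of moderate applies.

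**The concern.** For respiratory rate and PaO2/FiO2, the limits in criterion 5(b) are exactly the limits of the severe classes in Section 9.1. A patient who is not moderate on either of these at baseline can only be milder. SpO2 is the exception: one patient can be moderate by the entry rule and severe by the endpoint scale.

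The consequence falls on the mortality model. A two-level SpO2 term is useful only if its levels separate higher from lower risk. If the cut-points differ between sections and the model names neither, two programmers could code the term differently, and neither coding would distinguish the most hypoxemic patients from all the others.

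**Working it through.** **Inputs**
- Entry rule: Section 5.1.1, criterion 5.
- SpO2 and PaO2/FiO2 classes: Section 9.1.
- PaO2 from saturation: Appendix 3 ("Estimating PaO 2 from a given SO 2"): 80% → 44, 86% → 52, 90% → 60, 93% → 69 mmHg.
- FiO2 on oxygen: Appendix 3, which starts at 0.24. FiO2 in room air: 0.21, an assumption not stated in the protocol.

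The plan gives no figure of its own on this point. The nearby power statement in Section 11.4 reproduces. For 0.4 against 0.10 with 30 per arm, SE = √(0.24/30 + 0.09/30) = 0.105, and Φ(0.30/0.105 − 1.96) ≈ 81.6%, against at least 80% stated. Nothing here depends on it.

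**1. Does criterion 5(b) remove low SpO2?** Ratio = PaO2 / FiO2.

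| SpO2, room air | PaO2/FiO2 (mmHg) | Criterion 5(b) limit above 100 | SpO2 class, Section 9.1 |
|---|---|---|---|
| 80% | 44/0.21 = 210 | passes | severe |
| 86% | 52/0.21 = 248 | passes | severe |
| 90% | 60/0.21 = 286 | passes | severe |

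Every tabulated value from 80 to 90% passes if the respiratory rate is below 30/min, and all of them are mild on the protocol's own hypoxemia scale.

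On oxygen the gap narrows. A measured 86% at FiO2 0.50 gives 52/0.50 = 104 and passes. A measured 90% at FiO2 0.60 gives 60/0.60 = 100 and fails. From 0.60 upwards no measured value of 90% or less passes. The protocol's worked pair behaves differently. A reading of 93% on oxygen, treated as 86-87% in ambient air, gives 69/0.60 = 115 and passes, and first fails at 0.70 (69/0.70 = 98.6). Section 9.1 does not say whether its classes refer to the measured or the ambient-air value.

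**2. Does this reach the primary endpoint?** Sections 8.1.1 and 11.5.1 count as failure a rate of 30/min or more, an SpO2 fall of more than 5%, PaO2/FiO2 of 100 mmHg or less, or death by Day 4. None of these uses the Section 9.1 SpO2 classes. A patient who enters at 88% meets no absolute failure threshold through SpO2 and can still fail on any component.

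**3. What does the SpO2 covariate mean?** The model's wording supports two readings. Status is the term Section 9.1 uses for its classes. Moderate respiratory distress is the term of criterion 5.

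| Reading of moderate | Moderate level | Other level |
|---|---|---|
| Section 9.1 class | 91-93% | 90% or less, together with above 93% |
| Entry criterion | 93% or less, so 91-93% together with 90% or less | above 93% |

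The level above 93% is not empty, because a patient can qualify on rate or PaO2/FiO2 alone.

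**4. Illustration, with assumed death rates** of 10% above 93%, 25% at 91-93% and 50% at 90% or less.
- Section 9.1 reading, with a share s of the other level at 90% or less: its rate is 0.10 + 0.40s. This is 18% at s = 0.2 and 42% at s = 0.8, against 25% for moderate. The two levels are equal at s = 0.15/0.40 = 0.375. With 30% instead of 50% for the lowest group, the range is 14 to 26%.
- Entry reading, with a share t of the moderate level at 90% or less: its rate is 0.25 + 0.25t, or 30% at t = 0.2 and 45% at t = 0.8, against 10%. The order is right, but 25% and 50% sit in one level.

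**5. Room for covariates.** Section 11.4 supposes "if the true death rate is assumed to be 0.4 in the placebo group, then a true death rate of 0.10 should be assumed" on active treatment, or 0.3 against 0.04. With 30 per arm that is 12 + 3 = 15 deaths, or 9 + 1.2 ≈ 10. The model has six terms (treatment, BMI, age and three components), so about 2.5 or 1.7 deaths per term. A term that orders risk badly is expensive here.

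**The case against.** An entry criterion and a secondary outcome scale need not share cut-points. Criterion 5(b) excludes exactly the two absolute failure thresholds of the primary endpoint. Because the SpO2 component is a change from baseline, no SpO2 floor is needed for patients to be failure-free at entry. That is correct.

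A reader might go further and infer that patients already in the severe SpO2 class cannot progress and so dilute the primary endpoint. The documents do not support this: such patients can meet every failure component, and randomisation protects the unadjusted comparison. A restricted primary analysis that leaves them out is therefore optional and not needed.

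A reader might also infer that the model certainly puts best and worst risks in one level, or that the mortality odds ratio is confounded. The first holds only under the Section 9.1 reading; under the entry reading the term is in the right order. The second does not follow, because treatment is randomised. The model also carries a PaO2/FiO2 term, so baseline oxygenation is not wholly unadjusted.

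Finally, Section 11.5.1 leaves full detail to the SAP, which was not available for this review and may define the term. The mismatch between sections and the two-level coding are nevertheless written in the protocol itself. Neither reading separates patients at or below 90% from all others.

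**Conclusion.** The concern holds as a minor point. The SpO2 limits in Section 5.1.1 differ from those in Section 9.1 and the synopsis, and the Day 40 mortality model inherits the ambiguity. In ambient air, criterion 5(b) does not exclude any tabulated SpO2 from 80 to 90%, given the assumed FiO2 of 0.21.

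The number of patients affected is unknown. If 10 to 30% of entrants were at or below 90%, an assumed range, that would be 6 to 18 of 60. The loss in the covariate also depends on assumed death rates: from a reduced gradient to none under one reading, and a merged upper-risk group under the other.

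The effect is confined to one covariate in a supplementary adjusted analysis of a secondary endpoint. The cost is mainly precision. The unadjusted primary and mortality comparisons stand.

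**What to change.** 1. Reconcile the SpO2 wording of Section 5.1.1 criterion 5, the SpO2 status definition in Section 9.1 and the synopsis, and the mortality model in Section 11.5.1. State whether the Section 9.1 classes use the measured or the ambient-air value. Which limit is clinically right is for the sponsor and the investigators; this review does not choose one.
2. In the Day 40 mortality model, replace the two-level SpO2 term by a single term: either the Section 9.1 class entered as an ordered score, or baseline SpO2 as a continuous value, with the protocol's ambient-air conversion for patients on oxygen. One term keeps the parameter count unchanged.

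The cost is a wording change and one recoded covariate. SpO2 is already recorded at screening and baseline (Sections 7.2 and 7.3), and eligibility need not change. The drawbacks are small: a linearity assumption on the score or the continuous value, and reliance on a conversion for which criterion 5 gives only one worked pair.
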